## **59 Study procedures and evaluation**

### **60 Study schedule**

A summary of the study schedule for each group is detailed in Appendix 1.

### **61 Sensitization**

Sensitizing the parents/guardians of potential study subjects will precede the formal recruitment period to ensure that parents with children of the necessary ages are aware of the trial as far in advance as is practical.

### **62 Community sensitization**

A series of meetings with key leaders within the local community including the Alkalo (village/community chief), representatives of women's and family groups, Muslim and Christian religious leaders and other community advocates will be undertaken at venues within the local community, generally identified by members of the community itself and also at the clinical trials site. During these meetings, details regarding the trial will be discussed and a chance given for questions to be asked to ensure everybody present gains a full understanding of the central purpose of the trial and other key information (e.g. risks and benefits) as outlined in the informed consent document. Following these meetings information regarding the trial is disseminated throughout the local community through well-established community networks. These meetings aim to ensure that all parents/guardians of potentially eligible children become aware of the trial and are thus encouraged to attend the Sukuta Health Centre, where recruitment will take place. The meetings also serve a critical role in

ensuring influential members of the community properly understand the trial and therefore that accurate information is passed on and misinformation is avoided.

### **63 Individual sensitization**

Members of the clinical trial team will also base themselves within the clinic where the routine EPI schedule is administered at the Sukuta Health Centre, in order to identify parents/guardians who have older children potentially eligible for the study. A member of the clinical trial team will discuss the study with parents/guardians who are provisionally interested and agree to receive additional information. The discussion will be based on the contents of the informed consent document (ICD) and a copy of the ICD will be provided to the parent/guardian at the end of the discussion.

Parents/guardians with potentially eligible children who are interested will be encouraged to discuss the study with their spouse and other family members as appropriate. Following individual sensitization of the parent/guardian, a member of the field team may provide information to other family members (particularly the spouse) either by telephone or through a visit to the subject's residence according to the preference of the mother. This ensures that a lack of English literacy does not preclude anybody the parent/guardian feels is important from gaining a proper understanding of the proposed trial (the ICD is written in English only – see 6.1.2).

### **64 Informed consent**

The exceptional circumstances under which a guardian rather than a parent can provide the consent are described in section 11.2. Parents/guardians will be allowed at least 24 hours from receipt of study information and sensitization prior to children being recruited into the study.

### **65 Provision of information – English literate parents or guardians of children**

In the case of parents/guardians who are literate in English, they will be provided with a copy of the ICD but a member of the clinical trial team will nonetheless review the contents of the ICD line by line in English to ensure all details are covered and that the subject has the opportunity to ask questions regarding any aspect of the trial.

Prior to undertaking the informed consent process, the member of the clinical trial team undertaking consent will confirm and document English literacy by asking the subject to read a section of the ICD and explain the meaning briefly. If there is any doubt regarding the adequacy of English literacy, consent will be undertaken in a local language in the presence of an impartial witness (see 6.1.2.2). Of note, if consent is undertaken in English and without an impartial witness, the whole process must be completed in English; additional use of a local language must not occur under these circumstances.

### **66 Provision of information – non-English literate parents or guardians of children**

The ICD regarding the trial will be written in English only. Although many subjects speak only local languages (e.g. Mandinka, Wolof and Fula), these languages are primarily spoken rather than written languages and extensive efforts to translate and back-translate ICD into local languages have proved to be unsuccessful. Thus, consistent procedures have been developed locally and are well established for the provision of trial related information to non-English literate subjects.

In the case of potential participants who are not literate in English but only in one of the local languages, a member of the clinical trial team fluent in the local language (as well as being English literate) will review the ICD line by line translating directly from the English ICD to the appropriate local language. In this case an impartial witness must be present throughout all elements of the consent process and must attest that the information on the ICD has been given accurately and in full. The impartial witness will also be required to sign the ICD to confirm that this has been the case (Section 6.1.2.4).

Impartial witnesses are not part of the clinical trial team and are not employed by the MRC. They are generally recommended through the local community and may, for example, be retired teachers or other professionals. A potential participant may, if preferred, bring their own impartial witness, for example an English literate relative. Procedures related to consent and the role of the impartial witness are provided in detail in the relevant MRC Unit The Gambia policy document.

## **67 Assessment of understanding**

Having reviewed the ICD line by line (section 6.1.2.1 and section 6.1.2.2) the parent/guardian of potential participants will be asked a standardized series of questions to assess their understanding of key information regarding the trial. The questions are asked by a different member of the clinical trial team from the individual undertaking the consent process.

A subject who fails to attain a pre-determined standard of correct answers will have all the information in the ICD reviewed with them again and the questions re-attempted. Failure to reach the required standard on a second occasion precludes enrolment.

## **68 Documentation of informed consent**

Informed consent for study participation will be documented on the signature page of the ICD. The option to consent for the future use of any residual samples on study completion will also be given on the same page but the provision of such additional consent is not required for participation in the main trial.

English literate participants will be required to sign the ICD as well as writing the time and date that they completed the ICD signature page.

Participants who are not English literate may thumb-print the ICD (although some participants who are not literate in English may still prefer to sign or mark the ICD both of which are also acceptable). In any of these cases, the impartial witness will complete the time and date portion of the ICD to confirm the time and date the thumbprint/signature/mark was provided. The impartial witness is then required to sign, time and date the ICD to attest to the fact that the information in the ICD has been provided to the participant in full, that an opportunity to ask questions has been provided, that the questions have been answered to the participant's satisfaction and that consent appears to be given freely. Finally, the person taking consent signs, dates and times the ICD.

A certified copy of the ICD is provided to the participant unless it is refused for some reason in which case it will be filed at the trial site. Such refusal must be documented in the subject's file so it is clear that the subject has been offered a copy. The original ICD is also filed at the trial site.

## **69 Confirmation of ongoing willingness to participate**

Written consent is obtained only at the first visit. However, an opportunity to ask further questions will be given to each visit and ongoing willingness to participate will be confirmed

verbally and documented. The presentation of a subject to the clinical trial site will be taken to represent the ongoing willingness to participate on the part of the parent/guardian in the event that another responsible carer brings the subject for a particular visit.

## **70 Screening and enrolment**

### **71 History**

A focused history based around inclusion and exclusion criteria will be obtained and documented in a structured CRF to establish eligibility for enrolment (see section 5.3).

### **72 Medical and drug history**

A medical history will be obtained by the investigator, sub-investigator or study nurse. Any abnormal findings requiring further treatment will be managed according to local practice or an appropriate referral made according to the nature of the condition. A lack of exclusion criteria will be confirmed.

All concomitant medications a child is receiving will be recorded in the CRF. Data on antibiotic use within the last month will also be collected and recorded. The use of concomitant medication, other than those considered exclusion criteria, does not preclude recruitment (see section 5.3.2).

### **73 Clinical examination, vital sign and anthropometry**

A physical examination is performed by the investigator or sub-investigator with particular focus on the inclusion and exclusion criteria set out for the study. All relevant positive and negative findings will be documented within the subject's clinical notes and key findings will be captured in the CRF. Any abnormal finding requiring further treatment will be managed according to local practice or an appropriate referral made according to the nature of the finding.

A subject's axillary temperature will be recorded at each visit, using a calibrated thermometer. At the same time points the respiratory rate and heart rates will be measured.

Height and weight will be measured and recorded at each visit using appropriately calibrated equipment. Calculate Z-score (a z-score of less than -3 indicated severe protein-energy malnutrition and is an exclusion criterion).

### **74 Inclusion and exclusion criteria checklist**

Eligibility against a defined inclusion and exclusion criteria checklist will be confirmed prior to final enrolment and documented in the CRF.

### **75 Final confirmation of eligibility and definition of enrolment**

Eligibility for enrolment will be confirmed on the basis of the above (Section 6.1.3). A child will only be defined as being enrolled in the trial once final confirmation of eligibility has been determined and randomization has occurred.

### **76 Randomization**

Randomization will be undertaken using pre-prepared sealed envelopes as described in section 3.2.1.

## **77 Clinical samples**

### **78 Blood sample**

Blood samples will be collected by trained personnel who have had their competency confirmed and documented according to the written procedures defined for the trial. See section 6.3.1.

### **79 Nasopharyngeal swab**

Nasopharyngeal swabs will be collected by trained personnel who have had their competency confirmed and documented according to the written procedures defined for the trial. See 6.3.2.

### **80 Oral swab**

Oral swabs will be collected by trained personnel who have had their competency confirmed and documented according to the written procedures defined for the trial. See section 6.3.3.

### **81 Vaccination of children and immediate post-vaccination safety follow up**

All vaccinations will be administered by trained personnel who have had their competency confirmed and documented according to the written procedures defined for the trial. Written procedures describing the administrations of Nasovac-S will be used to ensure consistency of administration following appropriate training (see section 4.1.7.3).

All personnel administering Nasovac-S will be trained to recognize and manage anaphylaxis as appropriate in the clinical setting and no vaccines will be administered in the absence of the necessary resuscitation equipment as set out in the relevant written procedure.

### **82 Immediate post-vaccination observations**

Following vaccination with Nasovac-S, all children will be observed at the clinical trial site for 30 minutes. Vital signs (temperature, heart rate, respiratory rate) will be taken at the end of this period and all subjects will be assessed for local and systemic reactogenicity to confirm they are in stable a condition to go home. This period of observation may be extended if necessary based on the initial clinical assessment or vital signs.

### **83 [Unscheduled visits with possible influenza-like illness](#)**

All subjects in the study will be eligible for medical care at the clinical trial site from study entry until the 31st of October during the year of recruitment (i.e. at least 4 months, taking into account final date of recruitment during each period will be the 30th of June). Parents/guardians will be encouraged to attend with children in the study especially if they develop symptoms consistent with an influenza-like illness (symptoms of fever, cough or sore throat).

Clinical trial staff will complete a basic evaluation of symptoms and subjects who have received Nasovac-S as part of the study and fulfil the case definition below will have a NPS taken:

- Sudden onset of fever of  $\geq 38^{\circ}\text{C}$  (axillary) and
- Either a cough or sore throat

All subjects will be provided with medical care on site or referred on as appropriate according to clinical needs.

#### **84**    Procedures for obtaining clinical samples

All clinical samples will be obtained at the clinical trial site only.

#### **85**    Blood samples

5.0ml blood samples will be obtained from subjects at the time-points specified in Tables 1 and 3. Blood samples will be obtained by peripheral venepuncture from children by a doctor or nurse from the clinical field team following appropriate training and confirmation of competency against relevant study specific procedures governing this process. Blood will be collected into appropriate serum separation tubes, anti-coagulated blood tubes for cellular immunology assays and Paxgene® tubes for human transcriptomic studies respectively, depending on the visit (See Table 3). If blood volumes are limited, priority will be given to Paxgene® tubes, anti-coagulated blood tubes and serum separation tubes in that order.

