## 20 Study design

### 21 Type of study and design

All primary objectives and most exploratory objectives will be addressed through the conduct of a phase 4, randomized, controlled clinical vaccine trial. A total of 330 healthy children aged 24 – 59 months will be enrolled into one of three groups of equal size (3 x 110 children):

- (i) LAIV-vaccinated (Group A - blood sample at day 0, 2, 21)
- (ii) LAIV-vaccinated (Group B - blood sample at day 0, 7, 21)
- (iii) Control group (Group C)

Allocation concealment will be maintained from the start through the use of sealed envelopes. Block randomization stratified by sex will be used and a randomization sequence will be generated by an MRC Statistician not involved in the study. Investigators will not be blinded to group allocation from this point onwards as the sampling schedule differs between groups. Local laboratory staff will therefore not be blinded for this reason, but samples sent to external laboratories will be blinded (see section 3.2.3).

Two LAIV-vaccinated groups are included in order to achieve several exploratory objectives, which require blood sampling at different time points following vaccination, whilst minimizing the number of times children are bled times (i.e. 2nd blood sample at either day 3 or day 7 post-LAIV, but not both). The unvaccinated subjects will serve as a control group for the primary objective of assessing the impact of LAIV on the nasopharyngeal microbiome. Section 8 details the statistical considerations made to decide on the sample sizes to be recruited. The vaccination and sampling schedules for groups A, B and C are detailed in Tables 1.

Group C subjects will be administered LAIV after the NPS is taken on their day 21 visit, to offer them the same level of protection against influenza illness by participating in the study as those in groups A, B and D.

An additional 35 healthy children aged 24 – 59 months will be recruited in the 2nd phase of recruitment (Jan – June 2018) to assess the objective of how modulation of the nasopharyngeal microbiome with antibiotics impacts the mucosal immunogenicity to LAIV

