**Table 3. Sampling schedule and use of clinical samples in laboratory assays**

| Visit timing from LAIV
(window) | Clinical Sample | Laboratory assays                                                                                                                                                                                              |
|--------------------------------------------|------------------------|-----------------------------------------------------------------------------------------------------------------------------------------------------------------------------------------------------------------------|
| Day 0 visit                                | Oral swab              | Influenza-specific IgA and IgG                                                                                                                                                                                        |
|                                            | NPS^                   | Nasopharyngeal microbiome
Influenza-specific IgA
Host transcriptomic profiling
Viral multiplex RT-PCR                                                                                                        |
|                                            | Blood sample (5ml)     | Innate cell profiling (FC)
Influenza-specific T-cell responses (FC)
B-cell phenotyping (FC)
Peripheral T-follicular helper cells (FC)
Host transcriptomic profiling
Serum haemagglutination inhibition |
| Day 2 visit
(+ 1 day)                   | NPS                    | Host transcriptomic profiling
LAIV virus shedding (RT-PCR)                                                                                                                                                         |
|                                            | Blood sample (5ml)     | Innate cell profiling (FC)
Host transcriptomic profiling                                                                                                                                                           |

|                            |                    |                                                                                                                                                        |

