## 124 Planned analyses

### 125 Microarray data analysis:

These analyses will be conducted via collaboration with the [name] group (University of Edinburgh), facilitated by collaboration with [name] (University of Sao Paulo) and the MRC statistics and bioinformatics team.

Analyses will be conducted using Perl and Python scripts, R/bioconductor packages, as well as a broad range of tools and databases. Similar methods will be applied to both nasal and blood transcriptome data.

Microarray data will initially be normalized to background values and expression fold change calculated for each gene by comparison of day 2 with baseline values. Non-informative genes will be filtered out at a defined threshold of expression from baseline (e.g. 1.25-fold seen in at least 20% of vaccines [66]). Several independent statistical tests will be performed and only those significant in all tests taken forward for further analysis. Comparison of normalized data between groups (e.g. those with and without a  $\geq 2$ -fold increase in influenza-specific nasal IgA [7]) will utilize linear modeling of the  $\log_2$  scale expression values between groups and subsequent empirical Bayesian statistical testing with vertical p-value adjustment for multiple testing to control for false discovery rate. Pearson's correlation will be used to investigate relationships between fold-expression changes in genes and the magnitude of antibody or T-cell responses to identify probe sets that correlate with an immunological response [66].

Computational network-based approaches such as ingenuity pathway analyses will be used to examine relationships in the data using correlation of gene expression and biological relationships. Several groups have compiled compendia of coordinately expressed modules of genes and can be visualized as nodes linked by connections to other genes with correlated expression level. As such, vaccine responses can be analyzed basis of a number of co-regulated genes rather than individual expressed genes.

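### One blood-tube order for all bled groups ranks Group B's day 0 Paxgene tube, which has no later blood pair, above the baselines for Group B's own assays

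*Combined protocol and SAP*

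**What the plan says.** Section 85 (Blood samples) sets the draw: "5.0ml blood samples will be obtained from subjects at the time-points specified in Tables 1 and 3". It lists serum separation tubes, anti-coagulated tubes for the cellular assays and "Paxgene® tubes for human transcriptomic studies respectively, depending on the visit (See Table 3". The tubes thus vary by visit; nothing makes them vary by group. When blood is short the rule is: "If blood volumes are limited, priority will be given to Paxgene® tubes, anti-coagulated blood tubes and serum separation tubes in that order".

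Section 21 gives the bleeding schedule of the two randomized vaccine groups: "LAIV-vaccinated (Group A - blood sample at day 0, 2, 21" and "LAIV-vaccinated (Group B - blood sample at day 0, 7, 21". Table 2 has Group D bled at days 0, 2 and 21. Group C is not bled.

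Table 3, arranged by visit, puts blood transcriptomics at day 0 and day 2 and at no other visit. All day 7 blood assays are flow cytometry: "Peripheral T-follicular helper cells (FC"), influenza-specific T cells and B-cell phenotyping. The same three assays are listed at days 0 and 21, and serum HI at days 0 and 21.

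For the array data, section 125 plans "expression fold change calculated for each gene by comparison of day 2 with baseline values".

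**The concern.** A priority order matters only when something has to be given up, so the top-ranked tube should be the one whose loss would hurt the plan most. In Groups A and D, Paxgene first fits: those children also give day 2 blood, and gene expression change at day 2 is a primary endpoint. At day 0 in Group B it does not. The Paxgene tube has no later blood transcriptomic sample to be compared with, while the tubes ranked below it hold the baselines for that child's day 7 and day 21 assays.

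At stake are within-child changes in exploratory endpoints. Exploratory objectives (viii) and (x) ask whether cell populations expand after vaccination, which is most directly answered against the child's own baseline. The HI baseline serves within-child HI change and, through seroconversion, objective (xii). A day 0 sample that was not taken cannot be obtained after vaccination.

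**Working it through.** The plan states no figure for this rule, so there is none to reproduce. The check sets the schedule against the assay list and then sizes the loss under stated assumptions.

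**Step 1. Pairs available by group** (group sizes and bleeds from Tables 1 and 2; assays from Table 3)

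| Planned blood pair | Group A | Group B | Group D | Total |
|---|---|---|---|---|
| Transcriptomics, day 0 to day 2 | 110 | 0 | 35 | 145 |
| Cellular (pTfh, T-cell, B-cell), day 0 to day 7 | 0 | 110 | 0 | 110 |
| Cellular, day 0 to day 21 | 110 | 110 | 35 | 255 |
| Serum HI, day 0 to day 21 | 110 | 110 | 35 | 255 |

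Group B contributes no blood transcriptomic pair and every day 0 to day 7 cellular pair. Its day 0 to day 21 cellular and HI pairs are 110 of 255; the other 145 lie in Groups A and D. Group B does have a day 2 nasopharyngeal swab, so its nasal transcriptomic pair is unaffected.

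**Step 2. What a short draw loses.** Under the written order the serum tube is filled last and so is lost first. The anti-coagulated tube is lost when the draw V falls below P + C, where P is the Paxgene volume and C the anti-coagulated volume. With the anti-coagulated tube first, it is lost only when V < C. The protocol gives 5 ml in total but no volume per tube. Assumed splits, for illustration:

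| P (ml) | C (ml) | Cellular tube lost, order as written | Cellular tube lost, anti-coagulated first |
|---|---|---|---|
| 1.0 | 2.0 | V < 3.0 ml | V < 2.0 ml |
| 1.5 | 2.0 | V < 3.5 ml | V < 2.0 ml |
| 2.5 | 1.0 | V < 3.5 ml | V < 1.0 ml |
| 2.5 | 1.5 | V < 4.0 ml | V < 1.5 ml |
| 2.0 | 2.0 | V < 4.0 ml | V < 2.0 ml |

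The threshold falls from 3.0-4.0 ml to 1.0-2.0 ml.

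**Step 3. Size of the loss.** The short-draw rate is not in the documents. Assume 5-15%: 110 × 0.05 = 5.5, rounded to 6, and 110 × 0.15 = 16.5, rounded to 17. For the cellular pairs these counts are upper bounds, because by step 2 some short draws cost only serum. For HI, 6-17 of 255 planned pairs is about 2-7%.

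**Step 4. Effect on precision.** The smallest mean paired change detectable with 80% power at two-sided 0.05, in SDs of the paired difference, is (1.960 + 0.842)/√n = 2.802/√n:

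- n = 110: 2.802/10.488 = 0.267
- 5% lost, n = 104: 2.802/10.198 = 0.275
- 10% lost, n = 99: 2.802/9.950 = 0.282
- 15% lost, n = 93: 2.802/9.644 = 0.29

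If every short draw also lost the cellular tube, the detectable change would rise by about 0.01-0.02 SD.

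**The case against.** Four points can be made for the plan.

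First, Table 3 is arranged by visit and is not a group-by-group tube list. It places host DNA extraction only under day 2 blood, yet section 101 genotypes all 255 vaccinated children, including the 110 in Group B who give no day 2 blood. Tube handling may be settled in the study-specific procedures or the laboratory analytical plan, which are not part of these documents. That Group B fills a day 0 Paxgene tube is therefore a reading of the text. This stands as a caution. But section 85 ties the tubes to the visit and Table 3, with no exception for Group B, and the DNA entry suggests that Table 3 overlooked the group difference more than once.

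Second, a reader might infer that the Group B Paxgene sample is useless. The documents do not support that. Section 125 also plans between-group comparison of normalized expression without naming a time point, and section 130 plans open-ended integration of transcriptomic data with baseline and later responses. Either could use a baseline transcriptome. What can be said is that the planned fold-change analysis cannot use it, and that no stated objective or endpoint asks for it.

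Third, a reader might infer that every short draw loses the cellular baseline, or that none of the lost pairs has a counterpart elsewhere. The quoted order contradicts the former, because serum goes first. Step 1 contradicts the latter, because HI and day 0 to day 21 cellular pairs also exist in Groups A and D. A child without a baseline would still contribute day 7 and day 21 values, and the exploratory endpoints are worded as responses or frequencies at those days.

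Fourth, it is tempting to add that short draws fall on the youngest and smallest children, making the loss selective. That is plausible, but the documents contain nothing to show it.

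**Conclusion.** The point holds in a limited form. In a short Group B day 0 draw, the rule as written protects a tube that the planned blood analysis cannot use. It gives up first the child's HI baseline and then, if blood is short enough, the baseline for the cellular assays. The one loss that no other group can replace is the day 0 to day 7 cellular pair.

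The consequence is minor: the affected endpoints are exploratory, and at assumed short-draw rates of 5-15% at most 6-17 of 110 pairs are lost, with little effect on the detectable change. These figures rest on an assumed rate, and the volume thresholds on assumed tube splits. The mismatch between the order and Group B's schedule rests on neither. It does rest on reading Table 3's day 0 blood entries as applying to every bled group. The change is still worth making, because it is nearly free and the loss cannot be made good later.

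**What to change.** In section 85, make the order at day 0 group-specific: in Group B, the anti-coagulated tube first, then serum, with Paxgene last or omitted; in Groups A and D, the present order. Footnote the day 0 blood transcriptomics entry in Table 3 to match. If the sponsor wants a baseline blood transcriptome in Group B, state its purpose and why it outranks that group's own baselines.

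The cost is one sentence and one footnote, with no added visit, blood volume or assay. It is workable: Group C is not bled, so allocation must be known before the day 0 draw, and section 24 adds a group suffix to the identification number at randomization. Omitting the tube would save up to 110 Paxgene tubes. The downside is fewer, or no, baseline-only blood transcriptomes in Group B for the integration work in section 130.
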